### Recruitment

Recruitment will begin in March 2021. The MedPAC Quitline Service is promoted to Hong Kong residents through a variety of platforms, such as publicity and exhibitions in secondary schools and tertiary educational institutions, non-governmental organisations, and industries; community outreach activities; advertisements in newspapers, magazines, and on the Internet; the MedPAC Quitline website and social media platforms; posters; and snowball approaches. At least 20,000 pamphlets, booklets, and other publicity materials as well as invitation letters for this study will be delivered to secondary schools and tertiary educational institutions, including middle schools, vocational training schools, colleges, and universities. Exhibitions, carnivals, and anti-drug games and competitions will be held in secondary schools and tertiary educational institutions that agree to participate in this project. Our research assistant will screen all potential subjects and will invite those who meet the inclusion criteria to participate in the study.

### Randomisation and blinding

A simple complete randomisation method will be adopted. The subjects will be randomly allocated to either the intervention or the control group. The random numbers used for group assignment will be generated using a personal computer by another research assistant, who will not be involved in the subject recruitment. The randomisation will be performed by a research assistant who will open a serially numbered, opaque, sealed envelope that contains a card indicating the randomly allocated group. Because the subjects will be aware of their allocation according to the content received, we will be unable to completely blind them. However, a single-blind approach will be adopted, in which all outcome assessors and data analysts will be blinded to the group assignment.

### Intervention

In addition to receiving the basic service provided by the MedPAC Quitline, the subjects in the intervention and control groups will receive brief MI via IM interaction and general health text-messages, respectively.

#### Intervention group

The interaction communication using brief MI will be applied via the chat function of IM apps (e.g., WhatsApp or WeChat). The intervention will be performed for 6 months at a frequency of at least twice a week. To begin the conversation, trained peer counsellors will actively contact the participants and explore their lifestyles and their current barriers to and facilitators of change. The counsellors will do this by asking participants about their current lifestyles, drug-misuse habits, and levels of stress to establish a collaborative relationship with and obtain a general understanding of each participant (opening strategy). To further understand why a participant does not intend to reduce his/her drug misuse, the counsellor (interventionist) will review a typical day of the subject (a typical day) and ask about the advantages and disadvantages of not reducing drug misuse. Each participant will receive further information about the health benefits of reducing or quitting drug use, if he/she is interested in doing so (providing information). To elicit information on discrepancies, each participant will be encouraged to talk about his/her ideal future and to compare the past and the present (the future and the present). The interventionist will also listen to, explore, and summarise the concerns of the participant (exploring concerns). The interventionist will resolve the ambivalence of the participant by describing what others have done in a similar situation and presenting options, while not urging a participant to make a decision (helping with decision*-making*). Importantly, the participant’s confidence about reducing or quitting his/her drug use will be enhanced throughout the process of receiving personalised health advice, as this advice will emphasise the health benefits of reducing or quitting and encourage the participant to be aware of resources that enable and facilitate such behavioural change. At the request of the participant, the interventionist will provide more comprehensive information and suggestions on how to reduce drug use, including the skills to overcome withdrawal symptoms.

#### Control group

The subjects will receive general health information via text message, such as ‘do physical exercise for at least 30 minutes per week to keep yourself healthy’, for 6 months at a frequency of twice a week.

### Measures

The demographics and baseline characteristics of participants will be collected during the baseline phone counselling. A structured questionnaire will be developed for this purpose by adopting or modifying international and/or locally validated instruments. The questionnaire will gather information on a participant’s (a) drug misuse profile, including the types of drugs used, his/her number of days of use, his/her daily drug consumption, and his/her history of quitting; (b) beliefs and values relating to drug use, using the Chinese Drug Involvement Scale [19]; (c) drug misuse-related knowledge [20]; (d) attitudes towards their drug abuse [20]; (e) contemplation stage of drug-misuse abstinence, using the Contemplation Ladder Tool [21]; (f) treatment needs and motivation, using the Texas Christian University Motivation and Readiness For Treatment form [22]; (g) self-efficacy to avoid drug use, using the Adolescent Relapse Coping Questionnaire [23]; (h) quality of life, using the EuroQol 5-Dimension 5-Level Questionnaire [24]; (i) depression level, using the Center for Epidemiologic Studies Depression Scale [25]; and (j) self-esteem, using the Rosenberg Self-Esteem Scale [26]. The Chinese versions of the above scales have been evaluated to show acceptable validity and reliability [19–26].

All participants will receive follow-up telephone calls from our trained research assistant at 1 week, 1 month, and 3, 6, 9, and 12 months. During each follow-up telephone call, the participants will be asked to complete the structured questionnaire (Table 1). Participants who are lost to one follow-up will be contacted again in the next follow-up.

**Table 1 Tab1:** Schedule of enrollment and follow-up assessments

Assessment	Time-point						
	Baseline	1 week	1 Month	3 Months	6 Months	9 months	12 Months
Informed consent for participants	×						
Eligibility screen for participants	×						
Telephone counselling	×						
Sociodemographic characteristics	×						
Randomization	×						
Intervention	× (twice per week)						
Self-reported drug misuse	×	×	×	×	×	×	×
Attempt to quit	×	×	×	×	×	×	×
Chinese drug involvement scale	×				×		×
Drug misuse-related knowledge	×				×		×
Attitudes towards the drug misuse	×				×		×
Contemplation ladder	×	×	×	×	×	×	×
TCU MOTForm	×			×	×	×	×
Adolescent relapse coping questionnaire	×			×	×	×	×
EQ-5D-5 L level	×				×		×
Center for Epidemiologic Studies Depression Scale	×				×		×
Rosenberg self-esteem scale	×				×		×
Referral need and results	×	×	×	×	×	×	×

### Outcomes

The primary outcome will be changes in the participants’ reductions in self-reported drug consumption at 12 months compared to that at baseline. Secondary outcomes will be (1) changes in the participants’ reductions in self-reported drug consumption at 6 months compared to that at baseline; (2) 30 days self-reported drug abstinence at 6 and 12 months; (3) changes in relapse risk among the quitters at 6 and 12 months compared to that at baseline; (4) changes in the participants’ contemplation stages at 6 and 12 months compared to those at baseline; and (5) treatment needs and motivation at 6 and 12 months compared to those at baseline.

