**Methods:**

A two-group single-blind, randomised controlled trial will be conducted. Multiple approaches, including online and face-to-face methods, will be used to recruit the participants. The participants, aged 25 years or younger and reporting any drugs that they have taken within the past 30 days, will be recruited and randomised to receive either brief motivational interviewing via interactive instant-messaging (the intervention) or general health text-messages (comparator). The primary outcome will be the change in the participants’ reductions in self-reported drug consumption at 12 months compared to that at baseline. The secondary outcomes will be the changes in the drug-abusing participants’ reductions in self-reported drug consumption at 6 months, the changes in the drug-quitting participants’ 6- and 12-month contemplation stages and relapse risk compared to that at baseline, 30 days’ self-reported drug abstinence at 6 and 12 months, and the treatment needs and motivation at 6 and 12 months compared to that at baseline. The effectiveness of the proposed intervention will be examined with adjusted regression models, with adjustment for baseline characteristics and the use of an intention-to‐treat approach.

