### Participants and sampling

Callers to the MedPAC Quitline and those who are actively recruited from schools and communities will be eligible service targets for the MedPAC Quitline. Youth who misuse drugs and have contacted the MedPAC Quitline will be eligible for inclusion in this proposed study if they (1) are 25 years of age or younger, (2) report having taken drugs within the past 30 days, (3) are able to communicate in Chinese, (4) agree to receive counselling via a messaging app (such as WhatsApp or WeChat), and (5) verbally consent to join the follow-up intervention. We will exclude potential subjects who have communication barriers and those who are undergoing other drug-misuse recovery treatments.

Because no previous study has conducted a brief telephone-based MI intervention, the sample size for the proposed RCT has been calculated according to a previous RCT that involved a computer-based MI intervention [18]. In this previous RCT, the mean number of drug-misuse consumptions per day decreased from 11.94 at baseline to 5.52 at 12 months for participants in the intervention group, and 9.22 at baseline to 8.61 at 12 months for those in the control group. The effect size was 0.64 for the MI intervention on drug-misuse reduction, with reference to the control group [18]. Based on these results, to detect a two-sided significant difference between groups with a power of 80 % and a significance level of 5 %, which are commonly accepted metrics for behavioural studies, the required sample size for this proposed RCT has been estimated to be 40 participants in each group. Given an expected retention rate of approximately 60 % at the 12-month follow-up, the target number of participants will be at least 134 (67 per group).

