### Data analysis

Data analysis will be performed using the Statistics Package for the Social Sciences (SPSS) version 25.0 for Windows (SPSS Inc., Chicago, IL, USA). Analyses will be conducted on an intention-to-treat basis, with missing-value substitutions based on the last observation carried forward. A two-sided statistical significance level of 0.05 will be adopted for all analyses.

Descriptive statistics will be used to detail participants’ demographic characteristics and drug misuse profiles. Frequencies and percentages or means and standard deviations will be used to present categorical data and continuous data, respectively. The differences between intervention and control groups, in terms of sociodemographic factors and outcomes, will be compared using a chi-square test for categorical variables and by an analysis of variance for continuous variables.

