#### Main analysis

Odds ratios, risk differences, and 95 % confidence intervals will be used to compare the primary and secondary outcomes between the two trial groups. A generalised estimating equation model-based analysis will be used to summarise the intervention effect on the primary and secondary outcomes with and without adjustment characteristics, referral to a treatment institution, and the interaction times.

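### Change in relapse risk is compared between arms among quitters, a group most naturally formed after randomisation; the Abstract also limits contemplation stage to that group, while the Outcomes section does not

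*Protocol article*

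**What the plan says.** The Outcomes section of the protocol article gives secondary outcome (3) as "changes in relapse risk among the quitters at 6 and 12 months compared to that at baseline". Secondary outcome (4) is the change in participants' "contemplation stages at 6 and 12 months compared to those at baseline", with no restriction to quitters. Secondary outcome (2) is "30 days self-reported drug abstinence at 6 and 12 months".

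The Methods paragraph of the Abstract gives (3) and (4) one shared population. It lists "the changes in the drug-quitting participants" and then, for that group, "6- and 12-month contemplation stages and relapse risk compared to that at baseline".

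Under Participants and sampling, candidates must "report having taken drugs within the past 30 days". The Data analysis section states: "Analyses will be conducted on an intention-to-treat basis, with missing-value substitutions based on the last observation carried forward". The Main analysis section says that odds ratios, risk differences and confidence intervals "will be used to compare the primary and secondary outcomes between the two trial groups", and that a generalised estimating equation model will summarise the intervention effect on the same outcomes. Neither section exempts outcome (3) or calls it descriptive.

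Table 1 schedules the Adolescent Relapse Coping Questionnaire at baseline, 3, 6, 9 and 12 months and the contemplation ladder at every visit, with no restriction to quitters.

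**The concern.** Randomisation makes the arms comparable as randomised. It does not make comparable the subsets that later quit. If the intervention changes who quits, the quitters in the two arms are different kinds of people, and a difference in their relapse risk mixes any effect of treatment with that selection. Quitting is itself a listed secondary outcome, so the trial hopes for exactly the condition under which the comparison is distorted. Excluding randomised participants because of their response also cannot be squared with an intention-to-treat basis.

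The second issue is one of consistency. Contemplation stage has two populations in the same article, and a later report could cite either as the plan.

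**Working it through.** **1. When is the group formed?** Setting the passages side by side:
- At entry, everyone has used drugs within the past 30 days.
- The only abstinence measure is 30 days without use, by self-report, at 6 and 12 months.
- On that measure nobody is abstinent at entry, so membership is settled during follow-up. Outcome (3) itself ties quitters to 6 and 12 months.

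The term quitter is not defined, so this is an inference, although the most natural one.

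**2. Where do the two versions differ?**

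| Outcome | Abstract | Outcomes section |
|---|---|---|
| Relapse risk | quitters | quitters |
| Contemplation stage | quitters | all participants |

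The contradiction concerns contemplation stage only.

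**3. The plan's own design figure.** With effect size 0.64, two-sided 5% and 80% power, n = 2(1.96 + 0.842)²/0.64² = 38.3, so 39 per arm. The t-test version gives 39.3, so 40, as stated. Then 40/0.60 = 66.7, so 67 per arm, also as stated. This point does not dispute either figure.

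**4. How large could the selection effect be?** The article gives no quit rates, so every input here is an assumption. Let readiness be standard normal at baseline and follow-up, with correlation r between the two. Let the scale correlate rho with readiness at both times, with higher scores better. A participant quits if follow-up readiness exceeds a threshold. Treatment lowers the threshold and has no effect on the score.

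Mean follow-up readiness among quitters at quit rate q is phi(t)/q, where t is the normal quantile at 1 − q:
- q = 25%: phi(0.674)/0.25 = 1.271
- q = 10%: phi(1.282)/0.10 = 1.755
- difference: 0.484 SD

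The outcome is a change from baseline. Among these quitters mean baseline readiness is r times mean follow-up readiness, so the spurious difference in change is rho × (1 − r) × 0.484, in SD of the score:
- rho 0.5, r 0.5: 0.5 × 0.5 × 0.484 = 0.12 against the intervention
- rho 0.5, r 0.8: 0.5 × 0.2 × 0.484 = 0.05 against the intervention
- r = 1 (stable trait), or equal quit rates: zero

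Other quit rates at rho 0.5. The level bias is multiplied by (1 − r):

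| Quit rates | Level bias | Change, r 0.5 | Change, r 0.8 |
|---|---|---|---|
| 20% vs 10% | 0.178 | 0.09 | 0.04 |
| 30% vs 15% | 0.198 | 0.10 | 0.04 |
| 40% vs 20% | 0.217 | 0.11 | 0.04 |

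The direction also depends on the model. If baseline readiness decided quitting instead, mean change among quitters would be −(1 − r) times their mean baseline readiness. The same sizes would then favour the intervention.

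**5. How many would enter?** At 25% vs 10%, 67 × 0.25 = 16.8 and 67 × 0.10 = 6.7 of those randomised, or 10 and 4 of the 40 per arm expected to be retained. At 20% vs 10% of 40 retained, 8 and 4 enter. The standard error is then √(1/8 + 1/4) = 0.612 SD, and power for a difference of 0.64 SD is about 18% (normal approximation).

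**The case against.** **Quitter might be a baseline status.** Someone who stopped two weeks before enrolment meets the entry rule, Table 1 records quit attempts at baseline, and the Abstract's contrast between drug-abusing and drug-quitting participants could describe status at entry. A subgroup fixed at baseline would remain a randomised comparison. This stands as a limit: a reader might infer that the documents prove there are no quitters at entry, and they do not. It does not remove the problem, because the article states no baseline definition and the wording points to follow-up status.

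**A condensed article may leave the definition to the full protocol.** That is fair for the definition alone. The article itself, however, fixes the restricted population, the between-arm comparison and the intention-to-treat basis.

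**The bias may be small.** This stands. A reader might take the 0.484 SD gap in readiness levels as the bias. That would need a perfect scale (rho = 1) and baseline readiness unrelated to follow-up (r = 0). The outcome is a change, which removes any stable component.

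**Baseline values exist for later quitters.** This is correct, since Table 1 collects the questionnaire from everyone. The fault is the selected subset, not a missing baseline score.

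**The Abstract is only loosely worded.** Probably so, since it merges two outcomes in one clause and Table 1 supports the Outcomes section. It is still a contradiction to correct. A reader might infer that the two versions also disagree on relapse risk; they do not.

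**Conclusion.** The point holds with these limits. As written, the plan compares change in relapse risk between arms within a group most naturally defined by a post-randomisation outcome that the intervention targets. That comparison lacks the protection of randomisation and conflicts with the intention-to-treat statement. The Abstract and the Outcomes section also contradict each other on the population for contemplation stage.

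The size of the bias cannot be established from the article. Under the follow-up-readiness model with rho 0.5 and r from 0.5 to 0.8, it is roughly 0.04 to 0.12 SD against the intervention across the assumed quit rates. It may be nil, and under another selection model the sign reverses. The case for change therefore rests on the design fault, not on a demonstrated large bias. Only secondary outcomes are involved; the primary outcome and sample size stand.

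**What to change.** - Make the between-arm comparison of the relapse-related score in all randomised participants, adjusted for its baseline value. Name the measure. The relapse coping questionnaire is the obvious candidate, but the Measures section describes it as self-efficacy to avoid drug use, and nothing expressly links it to relapse risk.
- Define quitter, including the time at which status is judged. Label any quitters-only result descriptive and non-randomised.
- Align the Abstract with the Outcomes section, so that contemplation stage is analysed in all participants.

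A sustained-abstinence endpoint is not a substitute. It would score people who never quit the same as those who relapse, and so would replace the outcome rather than repair it.

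**Cost:** no new data, since Table 1 already schedules both instruments for everyone at baseline, 6 and 12 months. Changing the population of a declared secondary outcome is nevertheless a substantive amendment and should be documented before outcome data are examined. One small loss in meaning is that the all-participant score describes coping self-efficacy in current users as well as in quitters.

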### Data analysis

Data analysis will be performed using the Statistics Package for the Social Sciences (SPSS) version 25.0 for Windows (SPSS Inc., Chicago, IL, USA). Analyses will be conducted on an intention-to-treat basis, with missing-value substitutions based on the last observation carried forward. A two-sided statistical significance level of 0.05 will be adopted for all analyses.

Descriptive statistics will be used to detail participants’ demographic characteristics and drug misuse profiles. Frequencies and percentages or means and standard deviations will be used to present categorical data and continuous data, respectively. The differences between intervention and control groups, in terms of sociodemographic factors and outcomes, will be compared using a chi-square test for categorical variables and by an analysis of variance for continuous variables.

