#### Exploratory analysis

A subgroup analysis of the participants in the intervention group will be conducted using different IM apps and data on referrals to treatment institutions to determine whether the relative effects of study treatments vary significantly among subgroups of IM app users. Propensity score matching, including demographics and types of abused drugs, will be used to further determine the true cause-and-effect relationship between the intervention and control groups, with restrictions of these subgroups. Missing outcomes will be assumed to be dependent on observed data (missing at random), and the observed data will be analysed with a multiple imputation procedure to impute the missing values, as a sensitivity analysis.

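### Last observation carried forward is the main missing-data rule although about 40% loss is expected at 12 months; the multiple imputation already planned should take its place

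*Protocol article*

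**What the plan says.** The Data analysis section sets the general rule: "Analyses will be conducted on an intention-to-treat basis, with missing-value substitutions based on the last observation carried forward". The Main analysis section names a generalised estimating equation model and does not say whether it runs on filled-in data; the general rule implies that it does.

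The primary outcome (Outcomes) is "changes in the participants’ reductions in self-reported drug consumption at 12 months compared to that at baseline". The Intervention section runs both arms' programmes for 6 months, so the primary time point falls 6 months after they end. Participants receive "follow-up telephone calls from our trained research assistant at 1 week, 1 month, and 3, 6, 9, and 12 months" (Measures), and Table 1 marks self-reported drug misuse at baseline and at every call. Someone who misses a call is tried again at the next one.

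The sample-size text (Participants and sampling) allows for an "expected retention rate of approximately" 60% at 12 months.

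Under Exploratory analysis, outcomes are taken as missing at random and are to be "analysed with a multiple imputation procedure to impute the missing values, as a sensitivity analysis". The article gives no reason for ranking carry-forward above multiple imputation.

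**The concern.** Carry-forward (LOCF) answers the 12-month question only if nobody changes after the last contact. That sits badly with a trial whose outcomes are change in consumption, quitting and relapse risk. Six earlier values can stand in for the 12-month report: baseline (zero change), 1 week, and 1, 3, 6 and 9 months. All but the 9-month value come from before the programme, during it or at its end. The same rule covers "30 days self-reported drug abstinence at 6 and 12 months": someone who reports abstinence at an earlier call and is then lost would count as abstinent at 12 months.

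With about two values in five substituted, the primary estimate becomes a mixture of time points. Its error depends on when people are lost, whether loss differs by arm, and how each arm changes over time. Unequal loss is plausible, because one arm receives personal counselling and the other receives generic texts.

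**Working it through.** **Inputs from the protocol article.** Effect size 0.64, 80% power, two-sided 5%, 40 per group, 60% retention, 67 per group, 134 in total. The cited earlier trial fell from 11.94 to 5.52 (intervention) and from 9.22 to 8.61 (control).

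**Assumed, not in the article.** Timing and pattern of loss, course over time, within-person correlation 0.5, and SD of change 9.08. The SD comes from (11.94 − 5.52) − (9.22 − 8.61) = 6.42 − 0.61 = 5.81, and 5.81 / 0.64 = 9.08. The article does not say how 0.64 was standardised.

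**1. The plan's own figures.** A two-sample t-test at d = 0.64 needs 39.3, rounded up to 40 per group. Then 40 / 0.60 = 66.7, rounded up to 67, or 134 in total. All three reproduce.

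**2. Values substituted.** 0.40 × 134 = 53.6, about 54.

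**3. A building effect.** Let f be the share of the 12-month effect already present at the carried visit. With equal 40% loss, LOCF effect = (0.6 + 0.4f) × true effect.
- For f = 0, 0.25, 0.5, 0.75 and 1, a true d of 0.64 becomes 0.38, 0.45, 0.51, 0.58 and 0.64.
- Effect linear in time, permanent dropout spread evenly over the six calls: f = (0 + 0.23 + 1 + 3 + 6 + 9) / 6 / 12 = 0.267. Effect = 0.707 × 5.81 = 4.11, or 29% too small.
- Same course, each call missed independently with probability 0.4: f = (0.6×9 + 0.24×6 + 0.096×3 + 0.0384×1 + 0.0154×0.23) / 12 = 0.60. Effect = 0.839 × 5.81 = 4.87, or 16% too small.
- Simulated trials agree: 4.0 to 4.1 with permanent dropout (power 74–75%) and 5.0 with intermittent loss (14% too small, power 89%). Observed 12-month data gave 80–81% power.

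**4. A transient effect, with arms equal at 12 months.** False benefit = 0.4 × mean difference at the carried visits. A mean difference of 2.25 to 3.75 per day gives 0.9 to 1.5. Simulated false benefits lay in that range, with about 10–14% rejection. A stronger scenario (difference 0.64 SD to 6 months, 0.32 SD at 9 months, none at 12; correlation 0.6; dropout evenly over five visits) predicts 0.4 × (4×0.64 + 0.32) / 5 = 0.23 SD. Simulation gave 0.24 SD (about 2.2 per day at SD 9.08) and 26% rejection; observed 12-month data gave 0.01 SD and 4.8%.

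**5. Unequal loss, no effect.** If both arms improve by M by 12 months and f is the same in each, bias = (0.50 − 0.30) × (1 − f) × M. With f = 0.267 and M of 5 to 6 per day, this is 0.73 to 0.88 in favour of the better-retained arm. Simulations gave about 0.75 to 0.83 with permanent dropout and 0.40 with intermittent loss. If both arms instead improve early and then relapse, the sign turns: with 30% v 50% loss the bias was 0.14 SD against the better-retained arm, with 12% rejection.

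**6. The benign case.** With equal loss and the same course in both arms, LOCF was unbiased and rejected in about 4.5–5.4% of trials.

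Loss in these simulations did not depend on the outcome, so the observed 12-month data are unbiased there by construction. The trial itself has no such guarantee.

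**The case against.** Several points on the other side stand.

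- Re-contact after a missed call and the existence of a 9-month call mean that many carried values may be late ones. A reader might infer that 1-week or 1-month reports will typically stand in for 12 months. The article does not support that: it is possible but extreme.
- A reader might infer over-confident intervals because substituted values are treated as observed. In principle single imputation ignores that uncertainty, but the check does not show it: with no effect and equal loss the error rate stayed near 5%. The excess rejections above come from bias.
- A reader might infer that 40 completers out of 67 clashes with an analysis of all 67. It does not: the figures reproduce, and the proposed analysis needs the same allowance for loss. A certain loss of power does not follow either, since power rose with intermittent loss.
- Multiple imputation is pre-specified, so a divergence from LOCF would be visible. The fault is the ranking of the two methods and not the absence of a sound one.
- Missing at random may itself fail if relapse drives loss. It still uses the interim calls to predict the 12-month value, and does not fix that value at the last report.

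None of this gives a reason to make LOCF primary when 40% loss is expected.

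**Conclusion.** The concern holds as a matter of which method leads. About 54 of 134 primary values would rest on an assumption of no change that the article does not defend. The resulting bias has no fixed direction, so LOCF cannot be called conservative.

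The illustrative sizes are a false benefit of 0.9 to 1.5 per day from a transient effect, a 14–30% understatement of a building one, and a false difference of 0.4 to 0.9 with 70% v 50% retention and improvement in both arms. They rest on assumed courses, loss patterns, correlation and SD, and should be read as ranges and not as predictions. The bias disappears when loss is equal and both arms follow the same course. The sample size stands.

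**What to change.** Exchange the roles of the two methods. Make the missing-at-random multiple imputation now under Exploratory analysis the primary intention-to-treat analysis, with the interim calls, baseline and arm as predictors; a likelihood-based repeated-measures model is an equal alternative. Keep LOCF as a sensitivity analysis or drop it, and say which data the generalised estimating equation model uses. A sensitivity analysis for departure from missing at random is an optional addition and can be left to the analysis plan.

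The cost is two sentences, a little more analysis work and possibly wider intervals. Recruitment does not change: 67 × 0.60 = 40.2 observed outcomes per group, and 40 per group gives about 81% power at the planned effect size.

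### The change-from-baseline primary outcome has several unranked analyses at 0.05 and no named baseline-consumption covariate; one baseline-adjusted model should decide

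*Protocol article*

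**What the plan says.** - **Outcome.** The Outcomes section of the protocol article defines the primary outcome through "reductions in self-reported drug consumption at 12 months compared to that at baseline", which is a change from baseline.
- **Group comparison.** The Data analysis section covers outcomes as well as sociodemographic factors, and compares the arms "by an analysis of variance for continuous variables". No covariate is mentioned. The same section sets two-sided 0.05 for every analysis.
- **Main analysis.** "A generalised estimating equation model-based analysis will be used to summarise the intervention effect on the primary and secondary outcomes", and this is done "with and without adjustment characteristics, referral to a treatment institution, and the interaction times". The characteristics are not listed. The text does not say whether the adjusted or the unadjusted version decides, or whether the GEE response is the change, the 12-month value or the repeated values.
- **Abstract.** Effectiveness is to be examined by regression adjusted for baseline characteristics.
- **Available data.** The Measures section collects daily drug consumption at baseline, and Table 1 schedules self-reported drug misuse at all seven time-points.
- **Allocation.** "A simple complete randomisation method will be adopted", with no stratification described.

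**The concern.** Two problems arise.

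**Competing answers.** The primary outcome can be tested by analysis of variance, by an unadjusted GEE and by an adjusted GEE, each at 0.05. If they disagree, the protocol does not say which one answers the trial's question. A favourable version could then be chosen, or be suspected of having been chosen.

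**Unadjusted change.** Baseline consumption is likely to be a strong predictor of later consumption. The Discussion says that recreational users will be included, so baseline use should vary widely. Under simple randomisation in a trial of 134, the arms can differ at baseline by chance. A change score takes the whole baseline difference off the 12-month difference, whereas a baseline-adjusted model takes off only the part that the baseline-to-12-month slope supports. The change score is therefore less precise, and its estimate in any one trial moves more with a chance imbalance.

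The named adjusters do not solve this. Referral to a treatment institution and interaction times look like things that happen after allocation. If so, adjusting for them may remove part of the intervention's effect or bias the estimate.

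**Working it through.** **Inputs.** From Participants and sampling: effect size 0.64, 80% power, two-sided 5%, 40 evaluable per arm, about 60% retention, 67 recruited per arm. The reference trial's means there are 11.94 to 5.52 (intervention) and 9.22 to 8.61 (control). The correlation r between baseline and 12-month consumption is not given. I assume 0.3, 0.5 and 0.7, with equal SDs at the two times.

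**1. The plan's own figure.** A two-sample t-test at d = 0.64 needs 39.3, so 40 per arm. Then 40/0.60 = 66.7, so 67 per arm and 134 in all. The stated sample size reproduces, with no baseline covariate in it.

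**2. Precision.** Var(change) = 2(1 − r)SD². Var(baseline-adjusted) = (1 − r²)SD². The ratio of adjusted to change is (1 + r)/2.

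| Assumed r | Adjusted / change | Excess variance of change, 2/(1 + r) − 1 |
|---|---|---|
| 0.3 | 0.65 | 54% |
| 0.5 | 0.75 | 33% |
| 0.7 | 0.85 | 18% |

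**3. Chance baseline gap of at least 0.3 SD.** The standard error of the gap is √(2/n) SD.
- At 67 per arm (everyone analysed, last observation carried forward): √(2/67) = 0.173, z = 0.3/0.173 = 1.74, probability about 8%.
- At 40 completers per arm: √(2/40) = 0.224, z = 1.34, probability about 18%.

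**4. How much the choice can matter: the reference means.**
- Difference in change: (11.94 − 5.52) − (9.22 − 8.61) = 6.42 − 0.61 = 5.81.
- Difference at 12 months: 8.61 − 5.52 = 3.09.
- Baseline gap: 11.94 − 9.22 = 2.72, and 3.09 + 2.72 = 5.81.
- Baseline-adjusted: 3.09 + r × 2.72 = 3.91, 4.45 and 4.99 at r = 0.3, 0.5 and 0.7.

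**5. Cost of an open choice.** A simulation of 20,000 trials with 40 per arm and normal data compared analysis of variance on change with analysis of covariance. With no true effect, at least one was below 0.05 in 7.7%, 7.6% and 7.0% of trials at r = 0.3, 0.5 and 0.7. With a true difference of 0.64 raw SD, the two disagreed on significance in about 22%, 12% and 3%. The first result hardly depends on the sample size, because the two estimates correlate at √((1 + r)/2) whatever n is.

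**6. Power.** At 67 per arm and d = 0.64, nominal power is already about 96% unadjusted. If 0.64 is in change-SD units, it is 98% to 99.5% with baseline adjustment.

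**The case against.** The strongest reply is that a baseline-adjusted model is already planned and that the rest is detail for an analysis plan. Much of this stands, and it limits the point in several ways.

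- **A reader might infer that baseline adjustment is absent.** The Abstract promises it. Baseline consumption is unnamed, not excluded.
- **A reader might infer that analysis of variance on raw change is the primary test.** That sentence is in the paragraph on descriptive statistics and group comparisons, while the GEE stands under Main analysis. The section does not say that the GEE response is raw change. The precision loss in step 2 applies only to an unadjusted change comparison.
- **A reader might infer a large power problem from 40 per arm.** The plan is intention-to-treat with last observation carried forward, so 67 per arm enter, and step 6 shows little nominal power to gain. Carrying values forward may dilute the effect, but the plan gives no figure for that.
- **A reader might take the reference trial as showing regression to the mean.** Four means without SDs or a correlation show a baseline gap and nothing more. The arms also cross, which regression to the mean alone would not produce.
- **A reader might call the change score biased.** Under randomisation both estimates are unbiased over repeated trials. The difference is in precision and in how far one trial's estimate follows a chance imbalance.
- **The post-randomisation reading is not certain.** Table 1 records referral at baseline as well as later, and the meaning of interaction times is not defined.

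What the reply does not remove is the lack of ranking. The text itself tests outcomes by analysis of variance, runs the GEE two ways, applies 0.05 throughout and names none as deciding. The Abstract's promise makes this a matter to reconcile, not only a detail left out.

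**Conclusion.** The point holds as one of unranked analyses and an unnamed key covariate. It does not show that the trial lacks baseline adjustment or power.

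- An unadjusted change comparison carries 18% to 54% more variance than a baseline-adjusted one. This rests on an assumed r of 0.7 to 0.3 and equal SDs, and the loss shrinks as r rises.
- A baseline gap of at least 0.3 SD has a chance of about 8% at 67 per arm, or 18% among 40 completers per arm.
- Leaving the choice open between the change comparison and the baseline-adjusted one takes the false-positive rate from 5% to about 7-8%, a modest but avoidable inflation.
- The reference means show that the same data can give 5.81, 3.09 or about 3.9-5.0.

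The change should be made, since it is free and the baseline value is already collected.

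**What to change.** In Main analysis, name one primary analysis: the 12-month contrast in consumption between arms from the GEE, adjusted for baseline consumption as a continuous covariate and a short prespecified list of baseline-only covariates. State what the GEE response is, and bring the wording into line with the Abstract.

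Label the unadjusted GEE supportive. Remove significance tests of outcomes by analysis of variance from Data analysis. Keep referral and interaction times out of the primary model.

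The cost is analysis wording only. No new data, visits or participants are needed.
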